## Abstract

**Background:**

Cerebral palsy is the most common cause of physical disability in childhood. Spasticity is a significant contributor to the secondary impairments impacting functional performance and participation. The most common lower limb spasticity management is focal intramuscular injections of Botulinum Toxin-Type A accompanied by individually-delivered (one on one) physiotherapy rehabilitation. With increasing emphasis on improving goal-directed functional activity and participation within a family-centred framework, it is timely to explore whether physiotherapy provided in a group could achieve comparable outcomes, encouraging providers to offer flexible models of physiotherapy delivery. This study aims to compare individual to group-based physiotherapy following intramuscular Botulinum Toxin-A injections to the lower limbs for ambulant children with cerebral palsy aged four to fourteen years.

**Methods/Design:**

An assessor-masked, block randomised comparison trial will be conducted with random allocation to either group-based or individual physiotherapy. A sample size of 30 (15 in each study arm) will be recruited. Both groups will receive six hours of direct therapy following Botulinum Toxin-A injections in either an individual or group format with additional home programme activities (three exercises to be performed three times a week). Study groups will be compared at baseline (T1), then at 10 weeks (T2, efficacy) and 26 weeks (T3, retention) post Botulinum Toxin-A injections. Primary outcomes will be caregiver/s perception of and satisfaction with their child’s occupational performance goals (Canadian Occupational Performance Measure) and quality of gait (Edinburgh Visual Gait Score) with a range of secondary outcomes across domains of the International Classification of Disability, Functioning and Health.

**Discussion:**

This paper outlines the study protocol including theoretical basis, study hypotheses and outcome measures for this assessor-masked, randomised comparison trial comparing group versus individual models of physiotherapy following intramuscular injections of Botulinum Toxin-A to the lower limbs for ambulant children with cerebral palsy.

**Trial registration:**

ACTRN12611000454976

## Background

Cerebral palsy (CP) is the most common cause of physical disability in childhood with an incidence of 2.11 per 1000 live births [1]. It describes a “group of permanent disorders of the development of movement and posture, causing activity limitations that are attributed to non-progressive disturbances that occurred in the developing fetal or infant brain” [2]. In 2013, the Australian Cerebral Palsy Register reported that 71% of children with CP achieved ambulation and 91% were classified with spasticity as the predominant motor type. Children with lower limb spasticity often experience a range of impairments including weakness, tightness, reduced motor control and muscle selectivity. These impairments can lead to limitations in functional ability, balance, ambulation and fitness compared to typically developing peers [3,4]. Physiotherapy intervention focuses on reducing these impairments and optimising functional, goal-related performance.

Focal, intramuscular Botulinum Toxin-Type A (BoNT-A) injections to the lower limb are commonly used in combination with physiotherapy as the temporary reduction in spasticity provides an opportunity to facilitate rehabilitation outcomes [5-8]. For ambulant children with CP (Gross Motor Functional Classification System, GMFCS-E&R, Levels I-III [9]), there is strong evidence that injections of BoNT-A are safe and reduce muscle tone in spastic, active and non-fibrotic lower limb muscles for approximately 12–16 weeks [6,7,10-12]. BoNT-A impacts body structure and function, however the accompanying physiotherapy often targets activity level outcomes (International Classification of Functioning, Disability and Health, ICF [13]).

Functional improvement in ambulant children with CP has been reported in a number of randomised controlled trials (RCTs) comparing intramuscular lower limb BoNT-A injections with rehabilitation (physiotherapy, casting and/or orthotic management), to a control group of rehabilitation alone with or without placebo injections. Rehabilitation combined with BoNT-A injections demonstrated significantly greater improvement in gross motor function as measured by the Gross Motor Function Measure (GMFM-88 or-66) [14-18] and quality of gait using the Physician’s Rating Scale [14,19-22], Edinburgh Visual Gait Score (EVGS) [23] or Three Dimensional Gait Analysis (3DGA) [20]. Improvement in performance-related goals have been reported when measured by the Canadian Occupational Performance Measure (COPM) [17], Goal Attainment Scaling (GAS) [24] or parental questionnaires [15,16,25].

Despite the acknowledged success of physiotherapy rehabilitation combined with BoNT-A injections, relative effectiveness of the specific components of physiotherapy rehabilitation, including intensity and dose, is difficult to interpret because it is often poorly described [14,15,17,25]. Results of a number of systematic reviews and consensus papers found limited evidence to support or refute individual physiotherapy modalities post lower limb BoNT-A injections [5,7,11,26]. The content of physiotherapy rehabilitation outlined in reported studies has included: active and passive stretching of muscle agonists [16,18,22,23,27]; functional or resistive strengthening of the antagonists [16,18,22,23,27]; functional mobility training and/or gait training [16,18,23,27]. One retrospective, controlled intervention study has directly compared the specific content of two physiotherapy approaches following lower limb BoNT-A injections [28]. Thirty-eight children with CP (mean age 7 years, 7 months, GMFCS I-III, 11 unilateral, 27 bilateral motor distribution) who received Neurodevelopmental Treatment (NDT, mean total dose 24.2 hours) were randomly selected and retrospectively matched to a group of children who received conventional physiotherapy (CPT, mean total dose 20.5 hours). Content of physiotherapy, determined via therapist questionnaires, and improvement of impairment and gait-related goals (GAS) were compared between groups two months post injection. Both approaches utilized muscle tone inhibition techniques, stretching, strengthening and functional training, with the NDT group spending a greater proportion of time on functional training (NDT 42%; CPT 28%, *p* = 0.009). Whilst the NDT group showed greater goal attainment post intervention (mean converted GAS score NDT 56, CPT 52, *p* = 0.008), results should be interpreted cautiously. Therapy content was only described and analysed for 62% (n = 47) of children due to reduced completion of questionnaires by treating physiotherapists. As GAS goals were impairment-based it is unclear from this study if a more functional approach to training translates to improvement in goals related to function and participation.

In the absence of high level evidence, expert opinion and consensus statements recommend post BoNT-A physiotherapy includes functional and targeted motor training in combination with serial casting, stretching and strengthening [7,8,29]. Additionally, intervention should incorporate: (1) collaborative, individualized, realistic and specific goal setting which span across all domains of the ICF [7,29]; (2) specificity of task and training [30,31]; (3) repetition and practise within a functional “just right” context [32,33]; (4) environmental adaption [34] and (5) strategies to increase motivation and engagement [35,36]. This approach will facilitate rehabilitation focused on each child’s specific goals and functional needs [6,33,37]. Studies investigating the efficacy of physiotherapy combined with BoNT-A injections have consistently included therapy delivered in an individual model. It is unclear whether similar outcomes could be achieved using alternative methods of physiotherapy delivery.

Four models of therapy delivery have been reported in the literature for children with CP including: (1) individual (one on one); (2) group-based (three or more participants with similar abilities [38]); (3) web-based training or virtual reality [39,40]; (4) individual consultation with intervention performed as a home programme [41]. Group-based training has been shown to achieve positive rehabilitation outcomes through maximising engagement, motivation and participation [36,42]. Relative effectiveness of group versus individual physiotherapy post lower limb BoNT-A injections has not been examined to date, however. Independent of BoNT-A, effectiveness of group versus standard individualised care has been compared for ambulant children with CP receiving strength, endurance and fitness training [43,44], progressive functional strength training [45,46] and goal-directed activity-focused physiotherapy [47]. Results are difficult to compare due to the heterogeneity of theoretical focus, therapy dose and outcome measures used. However, these studies provide useful guidelines for the elements that contribute to successful group-based physiotherapy.

Effective group-based physiotherapy interventions report similar session structure including warm up, specific intervention activities and then warm down. To maintain motivation and specificity of practise, a combination of group-based activity and individual or paired circuit activity has been recommended [43,44,46,47]. To ensure adequate supervision and progression of exercises, group sizes have been limited to small (4–6 children) [44,45,47] or medium (7–9 children) [43]. Effective dose is not well understood due to variability in intensity, frequency and duration of intervention. Total direct therapy dose has varied from 36 hours [43,45] to 70 hours [44], delivered in varying intensity from three week blocks (intensive model) [47] to 34.6 weeks (distributed model) [44]. Individual session duration has ranged from 45 to 180 minutes with a frequency of two to five sessions per week. Indirect treatment dose achieved via home programme is difficult to interpret due to inadequate reporting. Despite insufficient evidence to confirm optimal group format, several studies found that group-based therapy can achieve equal or greater improvement in outcomes across ICF domains when compared to individual standard care. These include improvements in gross motor ability (GMFM-66) [43,44,47], crouch gait (3DGA) [48], participation (Children’s Assessment of Participation and Enjoyment: CAPE) [44], health-related quality of life (TACQOL) [44] and goal attainment (GAS) [47]. One RCT (n = 51) compared group-based progressive resistance exercise strength training to individualised standard care in 51 ambulant children with CP (GMFCS I-III; mean age 10y 5mo, SD 1y 10mo; 29 male) [45,46]. This study reported no improvement in either group for gross motor ability (GMFM-66), walking ability (One Minute Fast Walk Test) or participation (CAPE). No studies have reported inferior outcomes for group-based interventions compared to individual standard care. Additional qualitative benefits of a group-based model have been reported in the context of the self-determination theory [49,50]. A group program may enhance self-regulation and engagement in the therapy process by attending to children’s basic psychological needs for Autonomy, Relatedness and Competence. There is potential for greater promotion of autonomy by allowing choice (personal goal setting), and through enjoyment, having fun and behaviour modelling to master activities [36,51]. A sense of competence may be fulfilled through scaffolding activities to promote skill development, and providing opportunities for peer learning [52-54] and healthy competition [30,36]. Social support and working with children with similar needs may also increase the feeling of relatedness [36,55].

A group model has the potential to meet the physiotherapy rehabilitation needs for children post lower limb BoNT-A injections. To date there has been no study that has directly compared dose and content-matched group versus individual models of functional, goal-directed physiotherapy rehabilitation following lower limb BoNT-A injections for ambulant children with CP. This study aims to compare the efficacy of these two models to enable informed choice of post BoNT-A physiotherapy rehabilitation delivery.

## Methods/Design

### Study aims

This assessor-masked, parallel group, block RCT aims to compare group versus individual models of physiotherapy following intramuscular lower limb injections of BoNT-A for ambulant school-aged children with CP in the ICF domains of impairment (quality of gait, functional reach), activity/participation (caregiver/s perception of and satisfaction with their child’s occupational performance, gross motor function, walking efficiency) and quality of life [13]. A secondary aim is to gain qualitative feedback from treating physiotherapists, caregivers and participants involved in the study to determine acceptability of the two treatment models.

Study hypotheses are based on the reported benefits of a group model being at a participation and contextual level, so outcomes reflecting a child’s occupational performance, participation or quality of life may improve more in the group-based intervention. Individual training has the potential for greater intensity, specificity of training and repetition of practise of skills. Outcomes at the body, structure and function or activity level [13] could improve more with individual training. Consequently, the specific hypotheses to be tested are:

### Primary hypotheses

**H1:** Compared to individual physiotherapy, group physiotherapy will result in greater improvement in caregivers’ perception of performance of and satisfaction with their child’s occupational goal areas (COPM). This will be observed as between group differences of two or more COPM performance and satisfaction points at T2 (10 weeks-efficacy) and T3 (26 weeks-retention) [56].

**H2**: Compared to group physiotherapy, individual physiotherapy will result in greater improvement in quality of gait (mean score change of ≥ 4.0 points on the Edinburgh Visual Gait Score) at T2 (10 weeks-efficacy) and T3 (26 weeks-retention) [57-59].

### Secondary hypotheses

**H3:** Compared to group physiotherapy, individual physiotherapy will result in greater improvement in efficiency of gait (One Minute Fast Walk Test [60]), gross motor performance (Gross Motor Function Measure-88 Items D&E [61,62]) and functional balance (forward component of the Pediatric Reach Test [63]) at T2 (10 weeks- efficacy) and T3 (26 weeks- retention).

**H4:** Compared to individual physiotherapy, group physiotherapy will result in greater improvement in quality of life (Cerebral Palsy Quality of Life Questionnaire). This will be observed as a between group difference of five points or more in each domain at T2 (10 weeks- efficacy) and T3 (26 weeks- retention) [64-67].

### Study sample and recruitment

#### Inclusion criteria

The study will include children who:

1. Are aged 4–14 years at study entry;

2. Have a confirmed diagnosis of CP with a predominant motor type of spasticity;

3. Are ambulant (classified GMFCS-E&R Level I-III);

4. Are patients of the Queensland Cerebral Palsy Health Service (CP Health) BoNT-A program;

5. Require lower limb BoNT-A for management of spasticity interfering with lower limb functional goals;

6. Can commit to six weekly sessions of post-BoNT-A physiotherapy in either a group or individual format.

#### Exclusion criteria

Children will be excluded from the study if they:

1. Are unable to complete baseline assessments;

2. Have had orthopaedic or neurological surgery and/or other new spasticity management (e.g. Baclofen) within six months prior to commencing the study;

3. Have intellectual or behavioural difficulties which would limit their ability to participate in the assessment or therapy protocols;

4. Have medical co-morbidities which prevent them from exercising safely (e.g. cardiac or respiratory instability, uncontrolled seizures).

### Criteria for withdrawal/failure to proceed

Children will be classified as failure to proceed if they do not attend a minimum of four hours of direct therapy (<66%), or if they need to be withdrawn from the study due to significant post-injection or other medical complications requiring deviation from the rehabilitation pathway.

### Recruitment

#### Sample size

According to CONSORT guidelines, the sample size calculation is based on adequate power for comparison between the functional effects of group-based and individual physiotherapy intervention at 10 weeks (T2, immediately post intervention). A change score difference of two or more points between groups on the performance scale of the COPM (primary outcome measure) would be considered clinically meaningful [56]. A previous study of lower limb intramuscular injections of BoNT-A yielded a standard deviation of changes of 1.4 and 1.7 for COPM performance [17]. Based on a mean change of two points on the COPM performance scale and a standard deviation of 1.6 points for both groups, significance (alpha) level of 0.05 and 80% power, we require 24 participants (12 in each group). Allowing for 20% drop out, a total of 30 participants (15 in each group) will be recruited.

#### Randomisation

Eligible children will be recruited prospectively from the Queensland CP Health Service (Brisbane, Australia) BoNT-A injecting lists in blocks of four to eight children. For each recruitment period, participants will be evenly distributed into one of two geographical clusters according to residential address. Each cluster will be allocated to group or individual therapy by concealed random allocation. The random sequence will be created via coin flipping by an off-site, non-study researcher masked to all other study data. The outcome (e.g. 1 = group; 2 = individual) will be written on a piece of paper and concealed inside a sequentially numbered envelope and securely stored off-site. At each recruitment period the study coordinator will contact the off-site researcher to open the next consecutive envelope to reveal treatment allocation. At the end of each recruitment period, there will be close to equal numbers of children in each study arm. This process will continue until 30 participants are recruited.

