### Analyses

Statistical analysis will be undertaken by an investigator masked to group allocation (LS). Primary analysis will use the intention to treat principle, using the last observation carried forward for participants who withdraw before the end of the trial. Baseline data from each outcome measure for each treatment group will be reported using descriptive statistics. Continuous data will be compared between groups by fitting a regression model using generalized estimating equations [93] to baseline, 10 and 26 week measurements with an interaction term between the intervention group and a three-level factor indicating time of measurement. The generalized estimating equation model will assume a Gaussian family, identity link, and unstructured working correlation matrix for repeated measurements on participants. Conventional variance estimates will be used. Where continuous data exhibit skewness not overcome by transformation, non-parametric methods (Mann–Whitney U) will be used for simple comparisons. Statistical significance will be at p < 0.05 and analyses will be performed using STATA 11.

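### Small geographical clusters are randomised, but the sample size and the GEE treat the children as independent, so the stated 80% power and the 5% level are not assured

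*Protocol article*

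**What the plan says.** All references are to Methods/Design in the Protocol article.

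- **Randomisation.** Children are taken from the "BoNT-A injecting lists in blocks of four to eight children". Within each recruitment period, "participants will be evenly distributed into one of two geographical clusters according to residential address". Then: "Each cluster will be allocated to group or individual therapy by concealed random allocation". One envelope is used per period: "At each recruitment period the study coordinator will contact the off-site researcher to open the next consecutive envelope to reveal treatment allocation". No child is allocated individually.
- **Sample size.** The inputs are stated as: "Based on a mean change of two points on the COPM performance scale and a standard deviation of 1.6 points for both groups". The result, in the article's words, is: "significance (alpha) level of 0.05 and 80% power, we require 24 participants (12 in each group"). The recruitment target is then raised from 24 to 30 children, 15 per arm, for an expected 20% loss. There is no ICC, design effect or number of clusters.
- **Analyses.** A Gaussian GEE is fitted to the three time points with a group-by-time interaction and an "unstructured working correlation matrix for repeated measurements on participants. Conventional variance estimates will be used". Recruitment block and geographical cluster do not appear in the model.
- **Abstract and Study aims.** The trial is described as block randomised with parallel groups. It is not called cluster-randomised.

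**The concern.** The unit of allocation is a small cluster, while the unit in both the power calculation and the standard errors is the child. If children in the same cluster change more alike than children in different clusters, child-level standard errors are too small and the true information is less than 24 or 30 independent children would supply.

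Some within-cluster correlation is plausible from the article itself. Clusters are defined by where families live. Group-arm children attend the same sessions under one lead physiotherapist, and group dynamics are deliberately encouraged (Group therapy).

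The p-values for both primary hypotheses (COPM and gait score) are at stake, as is the 80% power for COPM performance. Where the error is anti-conservative, it favours declaring one delivery model superior when it is not.

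This is not a detail left to an analysis plan. The article itself fixes the allocation unit, the sample-size calculation, the correlation level and the variance estimator, and they do not fit together.

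**Working it through.** **Inputs from the article.** Difference 2.0 points, SD of change 1.6, alpha 0.05 (taken as two-sided), 12 evaluable per arm, 15 recruited per arm, blocks of 4 to 8 children in two clusters.

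**Inputs assumed.** ICC 0.05 to 0.20, equal in both arms, because the article gives none.

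**1. The plan's own figure.** For a two-sample t-test on independent children the noncentrality is 2 / (1.6 × √(2/n)). At n = 12 this is 3.06, and power on 22 degrees of freedom is 83.3%. At n = 11 power is 79.6%, so 12 per arm is the smallest number that reaches 80%. Dropout: 24 / 0.8 = 30. The stated figures therefore reproduce with a design effect of 1. (A one-sided test would need only 8 per arm by the normal formula and does not match.)

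**2. Number of randomised units.** 30/8 = 3.75 and 30/4 = 7.5, so about 4 to 8 blocks, the same number of coin flips, and about 8 to 16 clusters of m = 2 to 4 children.

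**3. Power.** The design effect is DE = 1 + (m − 1) × ICC and the noncentrality becomes 2 / (1.6 × √(2·DE/n)). Example: m = 4, ICC 0.20 gives DE = 1.60 and noncentrality 2.42 at n = 12. Power is 63.8% on 22 degrees of freedom. On 2 × (12/4) − 2 = 4 between-cluster degrees of freedom it is 45.4%.

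Each cell shows power from the design effect alone / with between-cluster degrees of freedom, 2n/m − 2:

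| m | ICC | DE | 12 per arm | 15 per arm |
|---|---|---|---|---|
| 2 | 0.05 | 1.05 | 81.5% / 76.8% | 89.7% / 87.0% |
| 2 | 0.20 | 1.20 | 76.2% / 71.2% | 85.5% / 82.3% |
| 3 | 0.05 | 1.10 | 79.7% / 68.4% | 88.3% / 81.5% |
| 3 | 0.20 | 1.40 | 69.6% / 58.2% | 79.8% / 71.8% |
| 4 | 0.05 | 1.15 | 77.9% / 57.9% | 86.9% / 74.3% |
| 4 | 0.20 | 1.60 | 63.8% / 45.4% | 74.3% / 60.4% |

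The 12-per-arm column treats dropout as loss of whole clusters. Dropout spread across clusters leaves more, smaller clusters, and power then lies between the two columns. The 15-per-arm column assumes that carried-forward values do not dilute the effect.

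**4. Type I error.** A child-level t-test at nominal 5% was simulated with 40,000 runs per setting and clusters × children per arm of 7×2, 5×3 and 4×4. It stands in for the GEE contrast at one time point. With all correlation at cluster level:

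| ICC | m = 2 | m = 3 | m = 4 |
|---|---|---|---|
| 0.05 | 5.6% | 6.1% | 6.7% |
| 0.10 | 6.3% | 7.6% | 8.6% |
| 0.20 | 7.3% | 9.8% | 12.5% |

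If half of the ICC is shared by both clusters of a block, the range over these layouts, plus 8×2, is about 4.9% to 6.5% at ICC 0.10 and 5.1% to 7.9% at ICC 0.20. If all of it is shared, the rate is about 3.1% to 4.5% over ICC 0.05 to 0.20.

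**The case against.** The strongest case on the other side is that the harm is conditional and may be small.

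- Clusters hold only 2 to 4 children. At ICC 0.05 the type I error is 5.6% to 6.7%, and design-effect power with 3 per cluster is 79.7%, in effect the stated 80%.
- Correlation common to both clusters of a block cancels between the arms, and leaving the block out then makes the child-level test conservative.
- The plan is intention to treat with last observation carried forward, so all 30 may be analysed. Design-effect power with 3 per cluster is then about 88% to 80%.
- Baseline is modelled as a repeated measurement, so stable differences between areas largely cancel. Only clustering of change matters.
- Individual-arm therapy is one-to-one, so an equal ICC in both arms is itself an assumption.

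All of this stands as a limit on size. It does not remove the mismatch: analysing all 30 does not correct the standard errors, and the article offers no ICC that would justify ignoring clusters.

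A reader might infer more than the article supports:

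- **That the true type I error must exceed 5%, or that the p-values are simply invalid.** This depends on the ICC and on how much of it is shared within a block, and neither is given.
- **That significance is out of reach.** With 5 blocks the smallest two-sided randomisation p-value is 2/2⁵ = 0.0625, but the protocol does not plan a randomisation test.
- **That power is poor even without correlation.** At ICC 0 the planned child-level comparison has 83.3% power. A lower figure there would come from choosing a cluster-level test.
- **That children in a cluster share a socio-economic setting.** The article mentions only residential address.

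**Conclusion.** The point holds in a conditional form. It is certain from the text that clusters are randomised, that the sample size has a design effect of 1, and that the analysis has no term for block or cluster. It follows that 80% power and a 5% level are not assured. It does not follow that both fail.

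The size rests on the assumed cluster-level ICC of 0.05 to 0.20 and clusters of 2 to 4. The lower end of that range is nearly harmless for the type I error, and the upper end, with four large blocks, is not. For power, the few between-cluster degrees of freedom are often the larger part of the loss, especially with clusters of 3 or 4. With 12 per arm and m = 4 at ICC 0.05, the design effect takes power from 83.3% to 77.9%, and the degrees of freedom take it on to 57.9%.

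**What to change.** 1. Describe the trial as cluster-randomised within recruitment blocks, and state the expected number and size of clusters.
2. Replace the conventional child-level standard errors with an analysis that accounts for recruitment block and geographical cluster on small-sample degrees of freedom. Two options are baseline-adjusted cluster means compared within block, or a mixed model with a cluster random effect and a small-sample correction. A cluster-robust variance without such a correction would be unreliable with 8 to 16 clusters.
3. Replace the flat 80% with a range of power over the assumed ICC and the number of blocks, saying whether 24 or 30 children are counted.

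**Cost.** The stated power becomes less favourable and confidence intervals widen, substantially so with few blocks. For a comparison within 4 or 5 blocks the t multiplier is 3.18 (3 degrees of freedom) or 2.78 (4), against 2.07 on 22. The ratios are 3.18/2.07 ≈ 1.53 and 2.78/2.07 ≈ 1.34, before any gain from pairing. No extra patients are needed for this restatement. Restoring 80% power across the whole ICC range would be a separate decision and could need more.
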